## Abstract

**Background:**

Radiofrequency ablation has been shown to be a safe and effective treatment for scar-related ventricular arrhythmias (VA). Recent preliminary studies have shown that real time integration of late gadolinium enhancement cardiac magnetic resonance (LGE-CMR) images with electroanatomical map (EAM) data may lead to increased procedure efficacy, efficiency, and safety.

**Methods:**

VOYAGE is a prospective, randomized, multicenter controlled open label study designed to compare in terms of efficacy, efficiency, and safety a CMR aided/guided workflow to standard EAM-guided ventricular tachycardia (VT) ablation. Patients with an ICD or with ICD implantation expected within 1 month, with scar related VT, suitable for CMR and multidetector computed tomography (MDCT) will be randomized to a CMR-guided or CMR-aided approach, whereas subjects unsuitable for imaging or with image quality deemed not sufficient for postprocessing will be allocated to standard of care ablation. Primary endpoint is defined as VT recurrences (sustained or requiring appropriate ICD intervention) during 12 months follow-up, excluding the first month of blanking period. Secondary endpoints will include procedural efficiency, safety, impact on quality of life and comparison between CMR-guided and CMR-aided approaches. Patients will be evaluated at 1, 6 and 12 months.

**Discussion:**

The clinical impact of real time CMR-guided/aided ablation approaches has not been thoroughly assessed yet. This study aims at defining whether such workflow results in more effective, efficient, and safer procedures. If proven to be of benefit, results from this study could be applied in large scale interventional practice.

*Trial registration*ClinicalTrials.gov, NCT04694079, registered on January 1, 2021.

## Background

Malignant ventricular arrhythmias (VA) represent “electrical abnormalities” of the heart that are the final result of several myocardial diseases and the leading cause of sudden death in cardiac patients [1].

Previous studies and meta-analyses [2, 3] clearly demonstrated that the presence of a myocardial scar is a significant predictor of sudden death, malignant arrhythmias or ICD shocks. The presence of isles and channels of viable myocardium represents the main pathological basis of most arrhythmia-related scars. Several triggers such as heart failure, molecular changes or autonomic nervous system unbalances have been considered important in the clinical development of arrhythmias [4]. Nevertheless, the substrate linked to jeopardized scar and viable myocardium constitutes the root of reentry circuits and, importantly, a major target for therapy. Every single subject will develop, after a myocardial injury, a specific pattern of fibrosis, with some individual, unpredictable characteristics (endo/epicardial involvement, confluent, jeopardized or merged fibrosis with normal tissue).

In the last decade, effort has been made to change the perspective of approach to VA and sudden cardiac death. ICD became the cornerstone of management; however, no event can be prevented by ICD, that effectively treats VAs only after their onset. Pharmacological therapy comprises only few drugs that interfere directly with the electrical properties of the myocardium usually with a single mechanism for every molecule. Unfortunately, major adverse effects of drugs limit their use and mitigate their benefit [5]. Consequently, percutaneous ablation becomes an important approach to prevent VA occurrence [6, 7].

The traditional approach to VT ablation implies the recognition of the origin and/or propagation of the myocardial signal during arrhythmia. Mapping of myocardial potentials during spontaneous rhythm or induced arrhythmias helps the physician to recognize possible foci or circuits for propagation. In a recent meta-analysis, the combined risk of ventricular arrhythmia recurrence and all-cause mortality during long-term follow-up was lower when using a substrate-based approach compared to standard ablation of stable VT. However, efficacy was greatly reduced if the substrate modification was incomplete [8].

Given the highly patient-specific pattern of myocardial fibrosis and the importance of a substrate-oriented approach, we highlight the opportunity to individualize the diagnostic and therapeutic strategies.

This goal can be attained by means of substrate identification, anatomic reconstruction (i.e., mapping of the fibrosis) and tailored modification. From a clinical point of view, cardiac magnetic resonance for the substrate characterization and radiofrequency ablation represent the mainstream “tools” to achieve the purpose.

The aim of the VOYAGE (Ventricular tachycardia ablatiOn and mYocardial scAr chracterization with maGnetic rEsonance) trial (ClinicalTrials.gov NCT04694079) is to test, in terms of efficacy, safety and efficiency, a tailored approach to VT ablation. The study will compare current standard of care with a tailored approach for VA radiofrequency (RF) ablation. The experimental approach is based on pre-interventional anatomic substrate definition by Cardiac Magnetic Resonance (CMR) with Late Gadolinium Enhancement (LGE), using a post-processing 3D elaboration software.

## Methods

### Study hypothesis and primary endpoint

Our hypothesis is that a comprehensive preprocedural individual characterization of the myocardial substrate via a CMR scan, and its integration within the mapping system can significantly improve technical intervention and patient outcome. The primary objective is to analyze the outcome of CMR guided/aided approaches of VT ablation in terms of effectiveness at 12 months in comparison to a control group (standard of care VT ablation). The primary endpoint is defined as any VT recurrences during a 12-months follow-up (not including the first month). VT episodes will be considered as recurrences if sustained (more than 30 s) or requiring appropriate ICD intervention and will be detected during outpatient clinic evaluation through an ICD interrogation.

Pre-specified group subanalyses will compare in terms of the primary endpoint:Patients with structural heart disease of ischemic originPatients undergoing endocardial-substrate only ablation

Secondary objectives are shown in Table 1.

**Table 1 Tab1:** Secondary endpoints

Secondary endpoints
Health-related quality of life changes
Procedural time (introducer in-introducer out)
Fluoroscopy duration
X-ray exposure
Radiofrequency time
Number of RF applications
VT inducibility at the end of ablation with number of residual VTs
Appropriate and inappropriate ICD interventions (ATP or shocks) anytime and after 1 month
Rate of patients with contraindication to CRM or with poor CMR imaging
Hospital admission for cardiac causes
VT storm anytime and after 1 month
Composite endpoint including death at any time, VT storm and appropriate ICD shock after 1 month of treatment
*Complications during 12-month follow-up*
Death (related or not to the procedure)
Myocardial infarction
Stroke or transient ischemic attack (TIA)
Other thromboembolic events
Cardiac perforation or tamponade
Vascular complications
Prolonged or repeat hospitalization
Heart block
Pericarditis requiring intervention
Pneumothorax
Pulmonary edema
Hepatic injury
Abdominal issues

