All patients who give informed consent for participation and fulfill the inclusion eligibility criteria will be consecutively enrolled (Inclusion and exclusion criteria are respectively shown in Tables 2 and 3). They will subsequently be evaluated for eligibility to CMR and CT. Patients with clinical or device-related contraindications to CMR or CT or with image quality deemed suboptimal for postprocessing will be assigned to Group 3 and undergo standard of care ablation. The other patients will be randomized in a 1:1 fashion to either Group 1 or 2 using a web-based platform. The scientific coordinator of the study or a delegate should be the unique responsible of randomization and will be contacted upon all new recruitments. LGE-CMR data obtained by 1.5 or 3 T CMR and multi-detector cardiac tomography (MDCT) data obtained using a 64 to 128 slice CT scanner will be processed with a specific commercial software (ADAS 3D, Galgo Medical, Barcelona, Spain). In Group 1, ablation will be performed based only on cardiac imaging information processed by the abovementioned software without electroanatomical mapping. A so-called anatomical approach is consistent with a previous observation [9] that ablation of channels only can be effective in preventing VA recurrences. In Group 2 ablation procedure will be based on information derived from both imaging and electroanatomic mapping data, but electrical CCs will remain as the final ablation target. Finally, Group 3 will be treated with standard ablation according to current clinical practice based on electroanatomic mapping (EAM). (Fig. 1).

**Table 2 Tab2:** Study inclusion criteria

Inclusion criteria
Indication for VT ablation in patients with structural heart disease (indications according to the 2015 ESC Guidelines for the management of patients with ventricular arrhythmias and the prevention of sudden cardiac death);
Structural heart disease (clinical history, ECG, multimodality imaging) involving the left ventricle
Signed informed consent;

**Table 3 Tab3:** Study exclusion criteria

Exclusion criteria
Age < 18 years;
ICD not already implanted nor expected within 1 month;
High probability of non-adherence to the follow-up requirements (due to social, psychological, or medical reasons);
Inability to give written informed consent;
Pregnancy (suspected or confirmed);
Acute coronary syndrome or PCI in the previous 30 days

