### Image processing

Images processing (ADAS 3D Galgo Medical, Barcelona, Spain) is pivotal to translate radiomics data produced by CMR into utilizable maps within the electrophysiology lab. Briefly, sequence packs created within each center will be transferred and processed by core-lab and finally elaborated by the software with the purpose of being integrated with the ablation mapping suite (CARTO 3, Biosense Webster, Diamond Bar, CA, USA). A pre-study phase for the achievement of quality standards in images acquisition has been accomplished in every center before the enrollment start date. The core-lab for image processing (U.O. Cardiologia 2—Azienda Ospedaliero Universitaria Pisana), will be further supported, if required, by Heart Institute in Teknon Medical Center (Barcelona, Spain). A VPN tunnel and an SFTP server will be used to securely transfer anonymized data between centers for post-elaboration.

LV endocardial and epicardial borders will be delimited by an experienced operator with a semiautomatic segmentation algorithm. Nine concentric layers will be identified from endocardium to the epicardium (10 to 90% of wall thickness). LGE-CMR information will be projected using trilinear interpolation over each layer surface and signal intensity distribution will be color-coded. Scar core (SC) and border zones (BZ) will be defined as 40% ± 5% and 60% ± 5% of maximum signal intensity respectively. Heterogeneous tissue channels (HTCs) will be defined as a corridor of BZ between two core areas or between a core area and a valvular annulus connecting two areas of healthy tissue.

The software will identify HTCs automatically, and they will be classified as:Sub-endocardial (layers from 10 to 50%).Sub-epicardial (layers from 60 to 90%).Transmural (layers from 10 to 90%).

Pixel signal intensity (PSI) maps and HTCs derived from LGE-CMR studies will subsequently be fused and aligned with the anatomical reconstructions extracted from multidetector cardiac tomography (MDCT) using the ADAS 3D software platform. This alignment allows the integration within the spatial reference coordinates of the mapping system by performing a fast anatomical mapping of the aortic root [9].

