### Ablation procedure

Ablation procedure will be carried out in an electrophysiology lab by using an electroanatomical mapping system (CARTO 3, Biosense Webster, Diamond Bar, CA, USA). An open irrigated 3.5 mm tip radiofrequency catheter (ThermoCool SmartTouch SF, Biosense Webster, Diamond Bar, CA, USA) will be used both for mapping and ablation.

In Groups 1 and 2 fast anatomical mapping (FAM) of the aorta from the aortic root to the origin of the left subclavian artery will be obtained in order to align such reconstruction with the MDCT-derived 3D model of the aorta and left ventricle, thus enabling the alignment between CARTO spatial references and post-processed CMR derived 3D model.

An electroanatomical map (EAM) of the target chamber will be obtained only in groups 2 and 3. EGMs will however be analyzed in all cases to avoid applications:At the level of His or fascicular EGMsAt the level of EGMs with an amplitude > 3 mV or 1.5–3 mV without delayed components, during sinus rhythm of after application of multiple extrastimuli to check for the presence of hidden slow conduction.

The target for RF ablation changes accordingly to the group of allocation or randomization.

Group 1: RF energy will be delivered at the entrance of HTCs identified in the maps created by images processing, regardless of the presence of any pathological electrogram (EGM) at such locations (Fig. 2). If VT is spontaneously induced, it’s allowed to map the circuit and ablate during tachycardia, even though it’s suggested to acquire the template and stop the arrhythmia (at first appearance) and continue the ablation of substrate.

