**Fig. 2 Fig2:**
[figure not shown]
Mapping suite showing a CMR-guided procedure, with VT interruption during RF delivery at an heterogeneous tissue channel **(**HTC**)** on 3D CMR model. Green: MDCT-derived aorta 3D model, blue areas: healthy tissue, red areas: scar tissue, yellow areas: border zone

Group 2 and Group 3: Ablation sites will be identified after analyzing the complete EAM, targeting conducting channel entrance-compatible EGMs, according to the “scar dechanneling” technique [10]. Other techniques aimed at achieving complete substrate ablation and currently used by the centre performing VT ablation, will be accepted. In case of absence of electrograms with delayed components at EAM, VT will be induced, and mapping will be done to delineate the circuit. In Group 2 the scar area localization via CMR images integrates the EAM data to help in substrate delineation focusing on that area. In Group 3 a complete left ventricle EAM will be achieved.

At the end of ablation, we will verify the absence of pathological EGMs and we’ll proceed towards inducibility test. In case of VT induction, we could have 2 scenarios: (1) hemodynamically tolerated VT: it will be mapped and ablated; (2) not hemodynamically tolerated VT: VT template will be taken and, after its interruption, used for pacemapping to identify VT exit site, which will undergo ablation.

Acute success will be defined as non-inducibility (2 drives, 2 sites, up to 3 extrastimuli) of any sustained monomorphic VT at the end of the procedure. Partial success will be considered with the clinical VT successfully ablated with other monomorphic VTs remaining inducible. Pre-ablation inducibility is not required and is discouraged unless in the abovementioned conditions.

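### One of the two pre-specified primary-endpoint subgroups is defined by the ablation performed, which follows allocation and is guided by different information in each group

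*Protocol article*

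**What the plan says.** Under Study hypothesis and primary endpoint, the article states that "Pre-specified group subanalyses will compare in terms of the primary endpoint" and lists two subgroups: ischemic structural heart disease, and patients "undergoing endocardial-substrate only ablation". The first is a baseline trait. The second is named by what is done at the procedure.

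The information that directs the procedure differs by group:

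- **Group 1** (Trial design): "In Group 1, ablation will be performed based only on cardiac imaging information processed by the abovementioned software without electroanatomical mapping". The Ablation procedure section adds, with reference to electrograms: "RF energy will be delivered at the entrance of HTCs identified in the maps created by images processing, regardless of the presence of any pathological".
- **Group 2** (Trial design): "In Group 2 ablation procedure will be based on information derived from both imaging and electroanatomic mapping data", with the electrical channels as the final target.
- **Group 3** (Ablation procedure): "In Group 3 a complete left ventricle EAM will be achieved". This group receives standard EAM-based ablation, and Table 4 schedules CMR for Groups 1 and 2 only.

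The only endocardial/epicardial classification described is in Image processing: "The software will identify HTCs automatically, and they will be classified as" sub-endocardial, sub-epicardial or transmural, by CMR layer. Group 3 consists of patients with a contraindication to CMR or CT, or with images not good enough to process. Sample size and statistical analysis applies intention to treat to the primary endpoint.

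**The concern.** A subgroup gives a fair comparison when membership is fixed before allocation, or at least cannot be affected by it. Here the assigned workflow helps decide where energy is delivered, and so who counts as endocardial-only. Two identical patients could be classified differently because they were in different groups. If epicardial involvement also changes the risk of recurrence, the endocardial-only patients in each group carry a different mix of risk, and a difference can appear with no effect of the workflow.

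This is separate from the non-random assignment to Group 3 and would remain if all three groups were randomised. It also reaches the one randomised contrast, Group 1 versus 2: both have CMR, but only Group 2 adds EAM and takes electrical channels as its target. Intention to treat fixes the arm in which a patient is analysed. It does not undo selection on something that happens after allocation.

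The analysis is one of only two named subgroups, it is on the primary endpoint, and the trial is open label. A favourable result could be presented as planned evidence.

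**Working it through.** **The plan's own figure.** With HR 2.75, 80% power, two-sided 5% and a 50:50 split, Schoenfeld's formula gives (1.960 + 0.842)² / (0.25 × (ln 2.75)²) = 30.68 events. The mean event probability is 0.5 × 0.16 + 0.5 × 0.44 = 0.30, so N = 30.68 / 0.30 = 102.3, rounded up to 103 as stated. This does not bear on the subgroup definition; it only supplies the scale of about 51.5 patients per side.

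**Model with no treatment effect.** The documents give no prevalence of epicardial substrate, no detection rates and no recurrence by substrate, so every input here is an assumption. Let

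- q = share of patients with truly endocardial-only substrate, the same in both groups;
- r_endo, r_epi = 12-month recurrence without and with epicardial substrate, the same in both groups;
- m = probability that a patient with epicardial substrate is still counted as endocardial-only.

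Recurrence in the subgroup is [q·r_endo + (1−q)·m·r_epi] / [q + (1−q)·m].

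The spurious gap (EAM minus CMR) is

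q(1−q)(m_EAM − m_CMR)(r_epi − r_endo) / {[q + (1−q)m_CMR]·[q + (1−q)m_EAM]}.

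Worked case: q = 0.70, risks 15% and 45%, m = 0.10 (CMR) and 0.50 (EAM).

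- CMR: (0.70 × 0.15 + 0.03 × 0.45) / 0.73 = 0.1185 / 0.73 = 16.2%
- EAM: (0.70 × 0.15 + 0.15 × 0.45) / 0.85 = 0.1725 / 0.85 = 20.3%

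| q | r_endo / r_epi | m CMR / m EAM | CMR | EAM | Gap (points) |
|---|---|---|---|---|---|
| 0.80 | 25% / 40% | 0.10 / 0.30 | 25.4% | 26.0% | 0.7 |
| 0.70 | 15% / 45% | 0.10 / 0.50 | 16.2% | 20.3% | 4.1 |
| 0.70 | 20% / 50% | 0.10 / 0.50 | 21.2% | 25.3% | 4.1 |
| 0.70 | 15% / 60% | 0.10 / 0.50 | 16.8% | 22.9% | 6.1 |
| 0.50 | 20% / 50% | 0.10 / 0.80 | 22.7% | 33.3% | 10.6 |
| 0.70 | 20% / 50% | 0.30 / 0.30 | 23.4% | 23.4% | 0 |
| 0.70 | 30% / 30% | 0.10 / 0.50 | 30.0% | 30.0% | 0 |
| 0.70 | 15% / 45% | 0.50 / 0.10 | 20.3% | 16.2% | −4.1 |

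Gaps are taken from unrounded rates. The 0.7 and 10.6 rows are the ends of a grid with q from 0.50 to 0.80, m 0.10 with CMR and 0.30 to 0.80 with EAM, and risk pairs 25%/40% and 20%/50%. As hazard ratios, ln(1 − EAM rate) / ln(1 − CMR rate), the ends are 1.03 and 1.57.

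**What the formula shows.** The gap is zero if the two workflows miss equally often, or if epicardial substrate carries no extra risk. It changes sign if EAM misses less than CMR. The same expression holds for Group 1 versus 2, with their own miss rates in place of m_CMR and m_EAM.

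**The case against.** - **Direction.** A reader might infer that endocardial-only patients in Groups 1 and 2 are the cleaner, lower-risk selection, so that the sub-analysis must favour CMR. The documents do not support this: no detection rate is given for either method, and no text says that a recognised sub-epicardial channel leads to epicardial ablation. Transmural channels include the endocardial layers. The miss rates above are therefore assumptions about both recognition and what the operator then does.
- **Overlapping information.** Groups 1 and 2 share CMR, and Groups 2 and 3 share EAM. In Group 1 electrograms are reviewed and spontaneous VT may be mapped. Some Group 3 patients will have had a scan that could not be processed, or a contraindication to CT only. It is therefore too strong to say that each group uses a different instrument, or that the patients certainly differ. What stands is that no single measure is available in all three groups.
- **Size.** In the worked case the subgroups hold about 51.5 × 0.73 = 38 and 51.5 × 0.85 = 44 patients. The standard error of the difference is √(0.162 × 0.838/38 + 0.203 × 0.797/44) = 8.5 points, so a 4.1-point bias is about half a standard error, against a planned contrast of 16% versus 44%. No power or decision rule attaches to this analysis, and the contrast with Group 3 is already non-randomised. This limits the harm but does not make the definition sound.
- **Condensed article.** The article does not say which groups the sub-analyses compare or how membership is recorded, and the full plan may. But the subgroup is stated, and stated by a feature that arises after allocation; that is not a missing detail. Reading it as patients whose substrate is endocardial only does not help, because substrate is still identified by different means across groups.

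**Conclusion.** The concern holds as a structural one. The subgroup is conditioned on a procedure that follows allocation and that the assigned workflow helps determine, so its comparison can be biased with no treatment effect, in the randomised Group 1 versus 2 contrast as well as against Group 3. Neither size nor direction can be fixed from the documents. If CMR leads to more epicardial substrate being recognised and treated than EAM does, and such substrate raises recurrence, the bias favours CMR, by 0.7 to 10.6 points over the assumed inputs; with the miss rates reversed it works against CMR. The main primary-endpoint comparison, the sample size and the ischemic subgroup are not affected by this point.

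**What to change.** **Group 1 versus 2.** Define the subgroup by the core-lab channel classification in Image processing: sub-endocardial channels only, versus any sub-epicardial or transmural channel. Complete and lock it before randomisation. Trial design shows that images are acquired and their quality judged before randomisation, but not that channels are classified by then, so the timing has to be written in. Failing that, and for patients already randomised, read the pre-randomisation images without knowledge of allocation.

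**Groups 1 and 2 versus Group 3.** No common pre-allocation measure exists. Report recurrence by ablation performed descriptively, with no test and no treatment-effect claim, and keep ischemic origin as the inferential subgroup.

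**Cost.** A short change to the protocol and analysis plan, one dated core-lab field, and blinded re-reading where the classification was not locked in time. Treatment and sample size do not change. The Group 1 versus 2 subgroup becomes an imaging-defined population, which is a somewhat different question, and one inferential subgroup comparison against Group 3 is lost.
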